### **3.4 Potential effect of these studies on the concepts, methods, treatments, services or preventative interventions that drive this field**

These studies will have a major impact on interventions to treat and prevent iron deficiency anemia in malaria endemic areas. The use of powdered mineral and vitamin fortificants is being scaled-up in a number of zero or low malaria burden developing countries as a means to prevent micronutrient deficiencies, including iron deficiency. Drs. [name] and [name] organized a one day symposium with the Ministry of Health of Ghana in 2006, including key United Nations agencies and NGOs. The government of Ghana has an Anemia Subcommittee dedicated to finding interventions to prevent anemia in Ghanaian children. The progress of the Subcommittee, however, has been markedly impaired by the results of the Pemba study and the subsequent UNICEF/WHO guidance on the use of iron in malaria endemic areas. The results of the proposed research study will provide the government of Ghana (as well as governments in other high malaria burden countries) with new and significant information for planning safe and effective anemia prevention programs.

## **4. PRELIMINARY STUDIES**

The Research Institute, Hospital for Sick Children in Toronto and the Kintampo Health Research Centre in Ghana have a long standing and collaborative working relationship. This provides the proposed project with a well-established and unique team of expertise in global health generally, and specifically in the area of iron deficiency anemia, malaria control and research (clinical trials) methodology.

Both Drs. [name] at the Kintampo Health Research Centre (KHRC) and [name] (Research Institute, Hospital for Sick Children and University of Toronto) have extensive experience as researchers in the fields of malaria and in infant and young child nutrition. [name], a professor of Pediatrics, Nutritional Sciences and Public Health Sciences at the University of Toronto has worked collaboratively with the Kintampo Health Research Centre since the late 1990s, originally with [name], Director at the time (now passed away) and for the past six years with [name] who has been the Director of KHRC since 2002. [name]'s original efficacy trials on 'Sprinkles' (a powdered mineral and vitamin fortificant) were completed at KHRC. The first collaborative manuscript was published in 2002 (29) the most recent publications from Ghana were published with [name] in 2006 (30, 35).

Sprinkles are sachets (like small packets of sugar) containing a blend of vitamins and minerals in powder form, which are easily sprinkled onto different foods. The single-serving sachets enable families without access to commercially fortified foods to add essential vitamins and minerals directly to traditional foods prepared in the home. They are inexpensive to produce, have no special storage requirements and are simple to use, even by those who cannot read. Because the iron is microencapsulated, there is no staining of a young child's teeth as may be the case with iron syrup or drops. A major advantage of the 'sprinkles' concept is that local foods can continue to be used and, thus, there is no need to teach caregivers how to prepare new and often expensive store-bought foods. Sprinkles were invented by the PI, [name], who, over the past ten years, has led a collaborative research team in multiple countries globally. Together these collaborative teams have demonstrated the absorption, efficacy, and effectiveness of microencapsulated iron, as well as the acceptability of the sprinkles concept (powdered minerals and vitamins) to treat and prevent iron and other micronutrient deficiencies (28, 29, 31, 35, 36).

As previously mentioned, the first randomized controlled trials were conducted in Ghana at KHRC. A total of 5 studies were completed at KHRC and published in peer-reviewed journals, including the American Journal of Clinical Nutrition and the Journal of Nutrition. More recently [name] has collaborated with a research team from the University of California at Davis (led by [name]), and partners at the University of Ghana at

Legon, to examine the relative merits of a powdered mineral and vitamin fortificant versus a fortified spread for the treatment and prevention of micronutrient deficiencies. Two recent publications describe that work (37, 38).

As well as having worked in Ghana with KHRC, [name] has experience with a number of other countries and research organizations. He has a long-standing research collaboration with the Research and Evaluation Division of BRAC in Bangladesh. He and his collaborators at BRAC have evaluated the effectiveness and acceptability of powdered mineral and vitamin preparations when provided on a weekly basis (versus daily) and with a flexible regimen (20, 39). [name] has also had successful research collaborations with the Chinese Centre for Disease Control (40), the Swiss Red Cross in Kyrgyzstan, World Vision International in Mongolia, CARE International in Benin (41), Agha Khan University in Pakistan (32, 42) and the King Edward Medical Hospital in India (25, 33, 43). In addition, he has collaborated with health economists to assess the cost effectiveness of 'point of use' powdered mineral and vitamin products (44). In northern Canada, powdered minerals and vitamins were examined in 'First Nations' populations (45-47). Powdered minerals and vitamins have also been used, in collaboration with the World Food Program, World Health Organization and Helen Keller International in relief situations (48).

[name] has beneficial interests in certain intellectual property rights to his invention known as "Sprinkles". These interests include (i) patent rights for the United States and Canada only, which are held by Ped-Med Limited, a Canadian corporation, of which [name] is the sole shareholder; and (ii) trade-marks rights in various jurisdictions to the name "Sprinkles" which are held either by Ped-Med Limited, or by the Sprinkles Global Health Initiative Inc. a Canadian not-for-profit corporation of which [name] is a member.

### **Global recognition of a 'powdered mineral and vitamin fortificant' as an important, new tool for improving the health of children**

The concept of using powdered mineral and vitamins packaged in a single-serving package has been recognized by international agencies such as UNICEF, the World Health Organization (WHO) and the World Food Program (WFP). Its success has been widely reported in both academic journals and the popular press. A number of government ministries of health have enacted legislation to include home fortification with powdered mineral and vitamin fortificants in recently updated national nutrition policies (Mongolia, Bolivia, Bangladesh, etc)

### **About the Kintampo Health Research Centre**

Kintampo Health Research Centre (KHRC) is a well-established, African-based, research centre. The mission of KHRC is to conduct public health research and develop health research capacity which will contribute to a significant reduction in ill-health and the achievement of the Millennium Development Goals for Africa's most disadvantaged communities. The African identity of KHRC is important as it emphasizes African solutions to African health challenges. KHRC is one of three field research centers of the Health Research Unit of Ghana Health Service established in 1994. KHRC is situated in the middle belt of Ghana in the Brong Ahafo Region with a mandate to serve health policy and practice throughout Ghana and Africa.

There are over 500 employees at KHRC. KHRC has over 12 years of extensive experience in health research in Ghana. Among many areas of activity in which it has demonstrated skill, knowledge and core competency it has developed one of the largest and most reliable district surveillance systems (DSS) and study populations in Africa. KHRC has an established reputation for quality research and personnel. KHRC is highly regarded and is the preferred partner of governments, organizations and donors in health research initiatives in particular large-scale health research trials. KHRC funding collaborators include government, bilateral and multilateral institutions, private corporations, private charities and international organizations from Africa, Europe, Canada and the USA

## **KHRC Priority Research Areas**

- Communicable diseases (CDs), particularly Malaria, TB and HIV/AIDS
- Sexual and Reproductive Health
- Maternal, Neonatal and Child Health
- Mental Health
- Non-communicable diseases (NCDs) such as hypertension and cancer
- Health Systems
- Using the DSS to track progress towards the Millennium Development Goals (MDGs) using indicators such as mortality levels, patterns and trends

Since 2003, [name] and his research teams at KHRC have characterized the epidemiology of malaria in the Kintampo area in the middle belt of Ghana (49-51). He has documented the incidence of malaria in children less than 5 years in this area as 7 attacks per child per year ([name] et al., in press). The transmission levels have been high throughout the year with an average inoculation rate of 269 infective bites per person per year ([name] et al., in press). [name] and his team of researchers are documenting the manifestations (both clinical and laboratory indicators) of severe and complicated malaria. Several antimalarials have been tested and evaluated in this area (52) and currently the most advanced malaria vaccine is being tested in Kintampo as one of several African countries. For more details on the KHRC laboratory and clinical facilities, please see pages 22-23 of this application (Resources Format Page).

The Kintampo Health Research Centre (KHRC) was awarded the 2008 Prince of Asturias Award for International Cooperation in recognition of its contribution to the fight against malaria in sub-Saharan Africa. The Prince of Asturias Foundation was formed by His Royal Highness, the Prince of Asturias, heir to the throne of Spain. It has conferred its awards since 1981. The awards are intended to acknowledge scientific, technical, cultural, social and humanitarian work carried out internationally by individuals, groups or in the categories of communication and humanities, social sciences, arts, letters, scientific and technical research, international cooperation, concord and sports.

The collaboration between the Research Institute at the Hospital for Sick Children in Toronto and KHRC in Ghana provides this project with a well-established and highly experienced team of experts in iron deficiency anemia, malaria control and Sprinkles-based research methodology. Given the past working relationship between the two partners, the protocol can be put into action without the need for preliminary relationship and trust-building activities between the two organizations.

## **Global Health at the University of Toronto, the Hospital for Sick Children and its Research Institute**

One of the strategic directions of the Hospital for Sick Children in Toronto is “to lead nationally and internationally”. Operationally this strategic goal is being met through programs within the Hospital, its Research Institute and its affiliation with the University of Toronto. For example, the Program for Global Pediatric Research at the Hospital was formed to address the disparity between the scientific research resources available in high-income countries and the quantity of scientific research focused on the health of children in mid- and low-income countries. This Program works at the centre of a global network to inform, educate, and facilitate international research cooperation and collaboration, as well as advocate for research to improve the health of all children. [name] is a member of that program.

The Research Institute at The Hospital for Sick Children undertakes child-centered research across the life continuum from fetal origins to adult outcomes, including fundamental discovery, applied research, and outcomes and impact. Support for clinical trials at the Research Institute is through the Clinical Research Support Unit (CRSU). This Unit is a consultation service operated by the Child Health Evaluative Sciences Research Program of the Research Institute. The mandate of the CRSU is to improve the quality of clinical

research at the Hospital by providing consultation in the areas of study design and methodology, statistical analysis, and data management.

[name] is Head of the Division of Gastroenterology, Hepatology and Nutrition at the Hospital for Sick Children, a Senior Scientist in the Research Institute in the Child Health and Evaluative Sciences Research Program, and a Professor (of Pediatrics, Nutritional Sciences and Public Health Sciences) at the University of Toronto. As a Professor, he has full access to the research facilities at the University. The University of Toronto is the largest university in Canada with more than 50,000 undergraduate students and 10,000 graduate students. It has more than 18,000 staff and faculty in 520 graduate programs and 42 professional programs. Its library system has over 18 million holdings, one of the top five research libraries in North America and its research grant and contract support is over \$800 million.

The combined infrastructure of the Hospital, the Research Institute and the University of Toronto provide more than ample infrastructure support for the collaborative project described in this application.

## 5. RESEARCH DESIGN AND METHODS

### 5.1 Design Conceptual or Clinical Framework

#### *Study Design*

The proposed study is a community-based blinded randomized controlled trial with 2 study arms that will be conducted in two phases:

- Phase I will take place during the dry season (December to April), when malaria transmission rates are lower. Eligible subjects (one per household) will be individually randomized to receive a daily dose of either a powdered vitamin/mineral fortificant containing 12.5 mg of iron (plus ascorbic acid, vitamin A and zinc), or a placebo (containing all micronutrients excluding iron), added to complementary foods, for 5 months.
- Phase II will take place during the wet season (June to October), when malaria transmission rates are higher. Eligible subjects, who did not participate in Phase I, will be individually randomized to one of the two study arms as described above and followed for 5 months.

A dual phase design, with two unique cohorts, was chosen so that preliminary results (at the end of phase 1) could be assessed by an independent Data Safety and Monitoring Committee. It is possible that during the dry season no impact of iron will be detected, while during the wet season, an impact will be observed. With this possible outcome, it is potentially feasible to translate this knowledge into a Ministry of Health Program to only provide iron supplementation (fortification) during the dry months of the year (December to April).

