We hypothesize that the incidence of malaria will be significantly higher in children receiving iron versus a placebo of micronutrients without iron. It was decided not to use the change in anemia status as a primary outcome since, in all previous studies with powdered mineral and vitamin fortificants, anemia rates declined compared to placebo controls, or were no different from the improvement in anemia rates observed with iron drops.

Based on the 2006 estimate of “cases and deaths from fevers suspected of being malaria” for children under 5 years of age in all of Ghana (53), the baseline rate of 3.44 episodes/child/year was assumed. We estimated that a total of 351 person-years would be required to detect a 15% increase in malaria incidence rates with 80% power and at a 5% type I error. Based on the experience and expertise of the PI and co-investigator, a difference of 15% in malaria incidence was considered to be clinically significant. Knowing that all children enrolled in the trial will begin the 5-month intervention period at a similar risk level, and accounting for 15% loss to follow-up, as well as the need to test the hypothesis twice (due to the interim analysis by the Data Safety and Monitoring committee), the sample size has been calculated as 1940 children per seasonal cohort (970 per group), or a total of 3880 subjects (see Table 1 below). All calculations were reviewed by 2 statisticians who will be involved in subsequent analyses.

Table 1: Sample size calculation adjusted for testing the hypothesis twice

| Least Meaningful Difference | 2006 rates  | Adjustment for use of bed-net | Rate unexposed | Rate exposed | Person-years | Follow-up years | n          | Loss to follow-up | Sample size per group* |
|-----------------------------|-------------|-------------------------------|----------------|--------------|--------------|-----------------|------------|-------------------|------------------------|
| 0.05                        | 3.44        | 0.75                          | 2.58           | 2.71         | 3017         | 0.42            | 7240       | 0.15              | 8326                   |
| 0.1                         | 3.44        | 0.75                          | 2.58           | 2.84         | 772          | 0.42            | 1854       | 0.15              | 2132                   |

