##### Primary analysis

The primary outcome, incidence of malaria, will be compared between the two groups using Poisson regression. A 95% confidence interval for the ratio between the incidence in the iron group and the incidence in the placebo group will be calculated. The upper boundary of this confidence interval will be compared to the 10% tolerance limit. If it is lower, then non-inferiority can be concluded.

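### Section 5.1 offers failure to detect an iron effect in the dry season as a possible basis for a dry-months-only programme, without requiring the protocol's own 10% limit or a comparison of the seasons

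*Protocol*

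**What the plan says.** Section 5.1 (Study Design) describes two separate cohorts: "Phase I will take place during the dry season (December to April), when malaria transmission rates are lower", followed by a wet-season cohort of different children. It then sets out one possible result: "It is possible that during the dry season no impact of iron will be detected, while during the wet season, an impact will be observed". In that event, it says, "it is potentially feasible to translate this knowledge into a Ministry of Health Program to only provide iron supplementation (fortification) during the dry months". It attaches no margin, confidence limit or between-season test to this inference.

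Section 5.5 (Primary analysis) does contain a criterion for acceptable risk, based on the 95% confidence interval for the iron/placebo incidence ratio: "The upper boundary of this confidence interval will be compared to the 10% tolerance limit. If it is lower, then non-inferiority can be concluded". Section 5.5 (Secondary analysis) applies the primary analysis to the Phase I data at the interim and says the study stops if malaria incidence is higher in one group.

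The sample-size text in Section 5.1 hypothesises a significantly higher incidence with iron and states that "351 person-years would be required to detect a 15% increase in malaria incidence rates with 80% power and at a 5% type I error". One annual, all-Ghana figure serves both seasons: "the baseline rate of 3.44 episodes/child/year was assumed". Section 4 (KHRC Priority Research Areas) reports a higher local figure: "He has documented the incidence of malaria in children less than 5 years in this area as 7 attacks per child per year".

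**The concern.** Not detecting an effect and showing that any effect is tolerably small are different findings. Section 5.1 uses the first as a possible basis for a seasonal programme, whereas Section 5.5 uses the second. The hypothesis and the sizing are both framed as detecting an increase, so the natural reading of no impact detected is a non-significant result. A dry-season interval of 0.98 to 1.19, for example, would show no detected impact but would fail the 10% limit.

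Non-detection is also easier in the season with fewer episodes. The less malaria there is, the more readily a real increase passes unnoticed. A second gap is that a non-significant result in one season and a significant one in the other does not show that the effect differs between seasons. What is at stake is how an inconclusive dry-season result in young children may be described to policy makers.

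**Working it through.** **Inputs**
- 351 person-years per group per cohort (Table 1). The text calls this a total, but the table converts it to 843 and then 970 children per group.
- Planning rate: 3.44 × 0.75 (bed-net factor) = 2.58 per child-year (Table 1).
- Tolerance limit: rate ratio 1.10 (Section 5.5). Clinically significant difference: 15% (Section 5.1).
- Local rate: 7 × 0.75 = 5.25 per child-year. Applying the bed-net factor to this figure is an assumption.
- Dry-season rate: not given. Half of each rate is used as an assumption.

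**Step 1. Reproduce the plan's figure.** PY per group = (z_α/2 + z_power)² (r0 + r1)/(r1 − r0)², with r0 = 2.58 and r1 = 2.58 × 1.15 = 2.967.
- Two-sided 2.5%: (2.241 + 0.842)² × 5.547/0.387² = 352, against 351 stated.
- Two-sided 5%: 291.

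Table 1 therefore uses about 2.5% per test. Then 351 × 12/5 = 843, and 843 × 1.15 = 970. The figure reproduces.

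**Step 2. Chance that a true rise is not detected in one cohort.** SE(ln RR) = √[1/(r0·351) + 1/(r0·RR·351)], and miss = Φ(z − ln RR/SE). At 2.58:
- RR 1.10: SE = 0.0459, miss = Φ(1.96 − 0.0953/0.0459) = 0.454.
- RR 1.15: SE = 0.0454, miss = Φ(1.96 − 0.1398/0.0454) = 0.132.

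Each cell gives two-sided 5% / two-sided 2.5%:

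| Dry-season rate per child-year | True +10% | True +15% |
|---|---|---|
| 2.58 (planning rate) | 45% / 57% | 13% / 20% |
| 1.29 (half, assumed) | 69% / 78% | 41% / 53% |
| 5.25 (local rate × 0.75) | 16% / 24% | 1% / 2% |
| 2.625 (half of 5.25, assumed) | 45% / 56% | 13% / 20% |

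Over-dispersion raises these. With a variance factor of 1.5 at 2.58, the 5%-level figures become 61% and 29%.

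**Step 3. What a non-significant result can still contain.** The largest upper 95% limit compatible with non-significance is about exp(2 × 1.96 × SE). That is exp(2 × 1.96 × 0.0459) = 1.20 at 2.58 and 1.29 at half that rate. Both exceed 1.10.

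**Step 4. The pattern of dry not detected and wet detected, with the same true effect in both seasons** (independent cohorts, two-sided 5%).
- +10%, both rates 2.58: 0.454 × 0.546 = 0.248.
- +10%, dry 1.29 and wet 2.58: 0.689 × 0.546 = 0.376.
- +15%, both rates 2.58: 0.132 × 0.868 = 0.115.

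**Step 5. The Section 5.5 rule applied to the dry cohort alone.** Pass = Φ((ln 1.10 − ln RR)/SE − 1.96).
- True RR 1.10: 2.5%.
- True RR 1.15 at 2.58: 0.2%.
- True RR 1.00 at 2.58: SE = √(2/(2.58 × 351)) = 0.0470, giving Φ(0.0953/0.0470 − 1.96) = 53%.
- True RR 1.00 at 1.29: 30%.

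**Step 6. Precision of a seasonal comparison.** With RR 1.00 dry, RR 1.15 wet and both rates 2.58, the log ratio of rate ratios has SE √(0.00221 + 0.00206) = 0.065. The 95% interval extends by a factor of exp(1.96 × 0.065) = 1.14 each way. Power to detect the difference is 57%. It falls to 45% if the dry rate is half, and the wet rate one and a half times, 2.58.

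**The case against.** The strongest reply is that Section 5.1 is not a decision rule. It describes a possible outcome and calls a seasonal programme potentially feasible. It defines no test, and significance is a reading of the word detected. This stands in part: a reader might infer that the protocol commits to a dry-season programme after a non-significant result, and the text does not say so. The reading is still the natural one, because the same section hypothesises a significantly higher incidence and sizes each cohort to detect an increase.

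The second reply is that the margin already reaches the dry-season data, because the interim analysis after Phase I uses the primary analysis. A reader might infer that no margin governs Phase I at all, and that would be wrong. But the interim is described for stopping. A cohort that does not trigger stopping proceeds to Phase II whether or not its upper limit is below 1.10, and nothing makes the seasonal conclusion depend on that limit.

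The third reply is that the local rate of 7 per child-year, reported with high transmission throughout the year, would make non-detection much less likely. That is correct and is shown in the table. If the dry season had half the net-adjusted local rate, the figures would return to about those at the planning rate.

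**Conclusion.** The point holds as a gap between two parts of the protocol. Section 5.1 treats non-detection in the lower-transmission cohort as a possible basis for a seasonal conclusion. Section 5.5 has a suitable criterion, but Section 5.1 does not invoke it, and no comparison between seasons accompanies the inference.

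For a true 10% rise, which is the protocol's own tolerance limit, non-detection is common at the planning rate: 45%, or 57% at the level Table 1 implies. It would be 69% at half that rate and 16% at 5.25. A reader might go further and infer that a 15% rise would often be missed as well. The documents do not support that. At the planning rate the miss is 13–20%, the lower figure at two-sided 5% and the upper essentially the designed 80% power. It falls to about 1% at 5.25, and reaches about 41% (two-sided 5%) only under an assumed halving of 2.58. The misleading seasonal pattern at +15% would arise only about 11% of the time at equal planning rates.

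These figures assume 351 person-years per group, Poisson variance and independent cohorts. The absent dry-season rate is the main uncertainty.

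**What to change.** Reword the closing sentences of Study Design in Section 5.1 along these lines: *A conclusion confined to the dry season will be considered supported only if, in the Phase I cohort analysed alone, the upper limit of the confidence interval for the iron/placebo malaria incidence ratio is below the 10% tolerance limit of Section 5.5. A non-significant dry-season result with an upper limit at or above that limit will be reported as inconclusive. Each season's rate ratio will be reported with its interval, and no difference between seasons will be claimed without a season-by-treatment comparison (ratio of rate ratios with interval).*

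This needs a few sentences and no additional children or data. The cost is that a dry-season safety claim becomes harder to reach: if iron truly has no effect, the cohort meets the limit only about half the time at the planning rate, and less often if dry-season incidence is lower (Step 5). The seasonal comparison will also be imprecise (Step 6), and the report should say so.
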